### Randomization and allocation

All eligible participants who provide written informed consent are randomly assigned to one of the two intervention arms (see also Fig. 1). The randomization is carried out weekly by the Center for Clinical Trials (University Leipzig) using a self-developed software, using the minimization algorithm by Pocock [36] stratified for gender (male/female), depression severity (mild/moderate according to PHQ-9 during screening), and CBT-experience (present/absent) with an 80% chance using the algorithm’s recommendation to yield well-balanced groups. This procedure guarantees to keep allocation concealed for the study assistants. After allocation, blinding is not possible, because study assistants also act as “guides” for the interventions during the study. We do not consider this a risk of bias, as the results are based on self-ratings only.

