Participants are encouraged to work with the tool on a regular basis. Each week, they are asked to read the information provided in the respective workshop and to use the corresponding exercise for at least one week. Participants can choose to complete worksheets online or to use a printed version if they find it more convenient.

The iFD® tool also incorporates a mood rating (PHQ-9, German version) with a graphical output display. It can be used as often as desired, but is mandatory once a week.

The iFD® tool was developed as a guided program; it was designed for complementing depression treatment in routine care. In the context of routine care, guidance is offered by physicians and licensed psychotherapists. Guides are required to complete a guidance webinar or face to face training and a short test before gaining access to the tool. They are instructed to focus on administrative and motivational support. Guides are motivating and positively amplifying participants and explore how well participants were able to integrate the practice into their daily routine.

For this study, the guides are trained psychologists and psychotherapists from the Research Centre of the German Depression Foundation. They have qualified through the webinar, are required to have a degree in psychology and are supervised by a senior psychiatrist who was involved in the development of the iFD® tool.

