#### Progressive muscle relaxation (PMR)

In the present study, progressive muscle relaxation (PMR) is used as an active control condition. It was chosen because it is widely used in therapeutic settings, e.g. as part of cognitive behavioral therapy and in the treatment of sleep disorders. PMR is also highly accepted by the public as a form of self-help for depression [28, 29] and rated as helpful by clinically depressed patients (38% very/moderately effective, 40% slightly effective [30]). In a systematic review, relaxation (PMR or similar techniques) was recommended as first line treatment in a stepped care approach. Antidepressant effects were visible shortly after relaxation interventions, superior to waitlist and no treatment, but inferior to psychotherapy [31].

The mechanism behind PMR was first described by Jacobson in 1934. He developed the concept to induce mental relaxation through relaxing the body. Muscle groups are tightened and then relaxed with the attention of the patient focused on the contrast between tension and relaxation. Through regular practice, a sensitization to tension in the body takes place and relaxation can be induced at will [38].

In the present study, PMR is used as the control condition. During the six weeks of training, participants are encouraged to practice PMR and learn how to deliberately induce physical relaxation to reduce stress and mental tension. Lessons range from 13 to 33 min and build on one another, adding more muscle groups every week. At the beginning of each week, participants receive a link to download the next lesson. They are instructed to practice on a daily basis, if possible, but at least two or three times a week and to integrate the practice into their daily routine.

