#### Secondary outcome

Secondary outcomes in this study are changes in depressive symptoms over the course of the intervention, acceptance (satisfaction with) and feasibility of the iFightDepression® tool, changes in perceived quality of life and adverse treatment effects (see Table 3).

**Table 3 Tab3:** Overview of assessment points and measurements used

Measurement time	Assessment													
	In−/exclusion criteria	Verbal consent	Sociodemographic data	Medical history, medication, therapies	M.I.N.I	PHQ-9 (Patient Health Questionnaire)	Written consent	IDS (Inventory of Depressive Symptomatology)	Content and subjective quality of guidance	Documentation AE/SAE	Evaluation of workshop/program + frequency of use	SF-12 (health related life-satisfaction)	INEP (assessment of side effects, adapted; modified for online usage)	CSQ-8 (patient satisfaction, adapted)
Online screening	P					P								
Telephone interview		P	SA	SA	SA	SA	P							
T0						P		P	SA	SA		P		
Week 1						P			SA		P			
Week 2						P					P			
T1						P		P	SA	SA	P	P	P	
Week 4						P			SA		P			
Week 5						P					P			
T2						P		P	SA	SA	P	P	P	P
T3–3 months						P		P		SA		P	P	
T4–6 months						P		P		SA		P	P	
T5–12 months						P		P		SA		P	P	

(P = patient, SA = study assistant)

Changes in depressive symptoms over the course of the intervention are measured with the nine-item Patient Health Questionnaire (PHQ-9). The PHQ-9 is a short, well validated and widely used measure, of which validity and sensitivity to change have been shown repeatedly [43, 44].

The acceptance and feasibility of the iFightDepression® tool is measured using the client satisfaction questionnaire (CSQ-8) in its German version (ZUF-8). Originally developed to measure client satisfaction with a therapy or service, an adapted version of the CSQ-8 is used to assess user satisfaction in the present study. The wording of some of the items has been adapted slightly to fit the context of web-based interventions. The internal consistency of a similar adaptation has been shown to be good (omega = .95) and ratings of satisfaction correlated with symptom reduction [45]. Four extra items, specifically designed for participants to rate different aspects of each workshop, were added. Participants also state whether they felt better after completing the last workshop and whether they attribute the change to the intervention or to other factors. Additional items at post-treatment ask participants to rate the entire intervention.

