### Quality assurance and data management

The study is designed in accordance with the declaration of Helsinki [49]. The study development and implementation is annually supervised by a scientific international expert advisory board and adapted towards their recommendations.

Procedures for data collection have been implemented by the Center for Clinical Trials at the University of Leipzig. Research data is collected in a pseudonymized manner by the Center for Clinical Trials. Data collection for online self-report measures as well as protocols completed by study assistants are centrally administered using LimeSurvey. The questionnaires are programmed in a way that all items have to be answered. The data are stored by the Center for Clinical Trials and will be provided to the research team upon request after the last patient finishes the intervention period and at the end of the data assessment period. Regular data-backups are performed.

Phone calls as described above are carried out to improve compliance with the interventions and online self-report questionnaires are installed to measure frequency and amount of intervention use. To keep the study procedures parallel across different study assistants, Standard Operating Procedures (SOPs) were developed and all study assistants are trained on the SOPs. Every Monday the study assistants receive feedback on the participants having filled out the questionnaires including the PHQ-9 sum score to check for deterioration or suicidality. At follow-up, patients are called again and, if necessary, reminded via email to fill out the respective questionnaire to assess possible adverse events during the follow-up period and to improve completeness of data. Patients reporting acute suicidality (score > 1 on the suicidality item of the PHQ) once or symptoms indicating severe depression (PHQ < 14) for three weeks in a row in the weekly questionnaires, or acute suicidality during the follow-up period are contacted using a well-established procedure to ensure appropriate clinical support.

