### Statistical analysis plan

Statistical reporting will follow the CONSORT standards [50].

For the main analysis, the mixed models approach with time and intervention group as fixed factors will be used to analyze whether there is a statistically significant difference between iFightDepression® and PMR concerning depressive symptoms after the 6-week study period, measured using the IDS-SR. A random intercept and a random slope for each participant will be added if beneficial for the model fit, with the subjects being nested within groups. This method is recommended in a scenario, where repeated measures are assessed over several time points and missing values need to be handled [51, 52]. All participant that are randomly assigned to one of the conditions are entered into the analysis (intent-to-treat = ITT-analysis).

Effect sizes will be calculated for imputed data (multiple imputations with 50 imputations) taking into account the dependence of data collected within participants to avoid the loss of power due to incomplete cases [53].

The number of patients experiencing a reliable change in each group will be reported giving an estimate on improvement/deterioration not attributable to chance taking into account the reliability of the measure [54]. For this calculation the standard error at the first point of measurement (T0) will be used, because it has not yet been influenced by any intervention.

Secondary analysis will include a per-protocol analysis (PPA - including all participants who adhered to the protocol), a repetition of the main analysis with outliers excluded, and a repetition of the analysis using the PHQ-9 results and a subgroup analysis, all using mixed models. In the subgroup analyses, possible moderating variables (e.g. gender, CBT-experience or frequency and length of logins) are going to be examined.

Changes in health-related quality of life (SF-12) will be analyzed, again, using mixed models, and differences in patient satisfaction (CSQ-8) will be confirmed using a *t*-test or a Mann-Whitney *U*-test, if normal distribution is violated.

An exploratory analysis of possible adverse events (INEP and protocols of the guidance calls) will be conducted. Frequencies of the occurrence of adverse events will be reported and compared between intervention group and control group using chi-sqaured tests.

Frequency and length of logins (according to self-rating) and the amount of guidance will be reported descriptively.

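### Self-rated login frequency and length are measured after randomisation but listed as moderators, so arm comparisons within usage levels can show moderation that is not there

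*Protocol article*

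**What the plan says.** The Statistical analysis plan section of the protocol article places a subgroup analysis among the secondary analyses, using mixed models, in which "possible moderating variables (e.g. gender, CBT-experience or frequency and length of logins) are going to be examined". The same section later adds: "Frequency and length of logins (according to self-rating) and the amount of guidance will be reported descriptively". That sentence adds a descriptive report; it does not withdraw logins from the moderator list.

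On how use is captured, Quality assurance and data management says that "online self-report questionnaires are installed to measure frequency and amount of intervention use". In Table 3 (under Secondary outcome), the column headed "Evaluation of workshop/program + frequency of use" is marked as patient-completed at Week 1, Week 2, T1, Week 4, Week 5 and T2. It is not marked at screening or T0.

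On delivery, the iFightDepression section says of the web tool's worksheets: "Participants can choose to complete worksheets online or to use a printed version if they find it more convenient". The PMR section says: "At the beginning of each week, participants receive a link to download the next lesson". No login is described for PMR, and the article defines the term for neither arm.

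Under Randomization and allocation, the minimisation factors are gender, screening PHQ-9 severity and CBT experience. The end of the Background states that subgroup differences are to be examined exploratively.

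**The concern.** A moderator analysis asks whether the treatment effect differs between kinds of patient. It has a causal reading only if the kind of patient is settled before treatment starts. Gender and CBT experience meet that condition. How often and how long a participant logged in over the six weeks does not, because it follows from the programme assigned and may also follow from how the patient was already feeling. High users of iFightDepression and high users of PMR may then be different sorts of people, and the difference between them mixes treatment with selection.

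The plan applies the right principle nearby: for reliable change it takes the standard error at T0, on the ground that no intervention has yet influenced it. That reasoning is not carried over to logins.

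At stake is the interpretation of the subgroup results. A finding that iFightDepression works in those who use it could appear, or be hidden, without any true difference in effect by use.

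**Working it through.** **The plan's own figure.** Inputs from the power analysis: difference 4 points on the IDS-SR, SD 11.1, alpha 0.05, power 80%. The normal approximation gives n = 2 × (1.960 + 0.842)² × (11.1/4)² ≈ 121 per group. The two-sample t-test gives 121.85, so 122, as stated. The 4 points and the SD of 11.1 are used below as a scale. Nothing here alters the sample size.

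**Timing.** Table 3 records use only from Week 1 to T2. Every usage value is therefore post-randomisation.

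**Size of a spurious subgroup effect.** Assumptions: improvement has SD 11.1 in each arm; use is normally distributed with the same distribution in both arms; its correlation with improvement is r_iFD in one arm and r_PMR in the other; there is no true moderation. The correlations are assumed, since the article gives none.

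- For a variable correlated r with use, the mean in the top half of use lies r × √(2/π) × SD above the arm mean, and √(2/π) = 0.798.
- The spurious arm difference in high users is (r_iFD − r_PMR) × 0.798 × 11.1 = (r_iFD − r_PMR) × 8.86.
- In low users it is the same size with the opposite sign, so the high-minus-low contrast is twice that.

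| r_iFD / r_PMR | High users | High minus low |
|---|---|---|
| 0.3 / 0.3 | 0 | 0 |
| 0.3 / 0.2 | 0.9 | 1.8 |
| 0.3 / 0.1 | 1.8 | 3.5 |
| 0.2 / 0 | 1.8 | 3.5 |
| 0.3 / 0 | 2.7 | 5.3 |
| 0.4 / 0 | 3.5 | 7.1 |
| −0.2 / 0 | −1.8 | −3.5 |

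As a share of the expected 4 points, 1.8 is 44% (1.77/4), 2.7 is 66% (2.66/4) and 3.5 is 89% (3.54/4).

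**False moderation findings.** A simulation (4,000 runs per setting) gave every patient the same 4-point benefit and tested an arm-by-use interaction in a linear model at two-sided 0.05. Group sizes were 122 (the stated requirement) and 180 (half of the 360 to be included).

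| r_iFD / r_PMR | 122 per arm | 180 per arm |
|---|---|---|
| 0 / 0 | 4% | 5% |
| 0.2 / 0.2 | 6% | 5% |
| 0.2 / 0 | 35% | 47% |
| 0.3 / 0.1 | 35% | 48% |
| 0.3 / 0 | 66% | 82% |
| 0.4 / 0 | 90% | 97% |

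At 0.3/0 the apparent effect was about 6.7 points in high users and 1.4 in low users, although the true effect was 4 in everyone. This agrees with the formula: 4 + 2.66 and 4 − 2.66. The simulation is a simplification of the planned mixed model and shows the mechanism, not a forecast.

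**The case against.** The strongest reply is that this is one example in a list for an exploratory, secondary analysis. No confirmatory claim rests on it, and the primary comparison of all randomised participants and the sample size are untouched. That stands, and it limits the weight of the point. It does not remove it: an exploratory label tempers claims of significance, but it does not make a biased comparison unbiased.

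Four stronger readings are tempting, and the documents do not support them.

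- **That false moderation will appear, in favour of iFightDepression.** It needs the usage–outcome correlation to differ between arms. Both arms are urged to practise regularly and receive the same guidance, so similar correlations are quite possible, and with equal ones the false-positive rate stays near 5%. The direction is not settled either: if early improvers stop logging in, the sign reverses.
- **That use is defined differently in the two arms.** This is an inference from delivery format. The questionnaires are described as covering intervention use in general, Table 3 has a single column for both arms, and the Discussion says PMR was chosen to match on time spent and frequency of use. A common question may exist. It would not cure the timing problem.
- **That screening severity has been left out as a moderator.** The list is given by way of example and excludes nothing.
- **That randomisation could serve as an instrument for completing workshops.** This needs assignment to have no effect in non-completers. The comparator is active and the article credits it with some antidepressant effect, so a non-completer assigned to iFightDepression also forgoes PMR. The condition is doubtful here.

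**Conclusion.** The point holds in a limited form. The article names a self-rated variable collected only after randomisation as a possible moderator alongside true baseline factors. Arm comparisons within its levels lack the protection of randomisation and can produce spurious moderation. This is a wrong choice stated in the text, not detail left to a fuller document.

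The size is conditional. With SD 11.1, a median split and the same distribution of use in both arms, the spurious effect in high users runs from 0 points when the correlations are equal to 3.5 points at 0.4/0, and it can be negative. Differing delivery formats (a web tool with optional printouts against a weekly download link) make unequal correlations plausible, but nothing in the article quantifies them. The consequence is confined to the exploratory subgroup results.

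**What to change.** Restrict the moderator analyses to variables fixed before randomisation, such as gender and CBT experience, and remove frequency and length of logins from that list. Keep the descriptive report of use, given by arm. If the relation between use and outcome is of interest, present it as a within-arm association that is labelled non-randomised, with use defined in the same way for both programmes and the definition stated.

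The cost is a change of wording in the analysis plan. No new data are needed, the sample size and primary analysis do not change, and the usage data already being collected serve the descriptive report.

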The current study’s goal is to fill some of the gaps in the current literature body on iCBT and to extend the evidence base for online interventions. It investigates the following objectives by evaluating the German version of the iFightDepression® tool (iFD®), a free-to-use, multilingual, guided online self-management tool that is based on the principles of cognitive behavioral therapy.

The primary objective of the study is to investigate the efficacy of the iFD® tool regarding changes in symptom severity compared to an active control group using progressive muscle relaxation (PMR) during a six week intervention period and at the follow-up assessments after 3, 6 and 12 months.

Based on the previous results on the efficacy of IBIs, we hypothesize that the iFD® tool will be superior compared to PMR in reducing depressive symptoms directly after the six weeks of intervention, and at follow-up.

The secondary objective is to examine possible negative effects, usability and satisfaction with the program and potential changes in health related quality of life (all assessed during the intervention period and at the follow-up assessments).

We hypothesize, that the iFD® tool will lead to a significantly greater improvement on quality of life, especially concerning mental well-being, than PMR and that both interventions will be equally usable and satisfactory for the users. Possible negative effects and subgroup differences will be examined in an explorative manner.

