**Fig. 1 Fig1:**
[figure not shown]
Participant flow, the numbers provided are the estimates based on the power analysis and dropout percentages in previous studies [35]. (DF = depression foundation, AE = adverse event, SAE = serious adverse event, PMR = progressive muscle relaxation, iFD® tool = iFightDepression® tool)

Power analysis to determine sample size:

For the power calculation, results of the study by Hegerl et al. were used to estimate the expected difference for the primary outcome between intervention and active control group in the present study [35]. The study compared CBT to an active control condition (guided self-help group) and found a difference of 5.3 points and a pooled standard deviation of 11.1 on the IDS-C after 10 weeks. Since the present intervention takes only 6 weeks and the effect sizes might generally be smaller for online self-management compared to face-to-face treatment, we expect a difference of 4 points on the IDS-SR. The calculation was performed in G*Power (3.1.9.2) using the power analysis for independent groups. To detect this effect with a power of 80% (alpha = .05), the number of cases needed per group is 122. Considering the expected dropouts, this trial is powered for completers.

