Analyses will be performed using an alpha level of .05, testing two-sided. All analyses will be conducted using SPSS [55] or R [56].

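### Satisfaction is hypothesized to be equal in the two arms, but the CSQ-8 is analysed only with a difference test, which cannot support equality

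*Protocol article*

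**What the plan says.** At the end of the Background, the protocol article states its hypotheses. One is that "both interventions will be equally usable and satisfactory for the users". The sentence after it marks what is exploratory: "Possible negative effects and subgroup differences will be examined in an explorative manner". Satisfaction is not on that list, so the equality statement stands as a study hypothesis.

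The Secondary outcome section lists "acceptance (satisfaction with) and feasibility of the iFightDepression® tool" among the secondary outcomes and names the CSQ-8 as the instrument. Table 3 shows the CSQ-8 collected once, at T2.

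The Statistical analysis plan section gives satisfaction one analysis: "differences in patient satisfaction (CSQ-8) will be confirmed using a" t-test, replaced by a Mann-Whitney U-test if the data are not normal. The general rule is "Analyses will be performed using an alpha level of .05, testing two-sided". The article gives no equivalence margin, equivalence test or confidence-interval criterion for the CSQ-8.

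**The concern.** The hypothesis and the test point in opposite directions. A two-sided t-test or U-test takes no difference as its null and looks for evidence against it. Here no difference is what the trial expects to find. A significant result would count against the hypothesis. A non-significant one would show only that the data did not exclude zero, which is also what a real difference estimated imprecisely looks like. The plan's wording, under which differences are to be confirmed, sits badly with a hypothesis of equality.

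This is not a detail that an article may leave to a fuller plan. The article names the test, and the named test does not fit the named hypothesis. What is at stake is whether any statement that the programs were equally satisfactory would have support from the planned analysis. As written, it would not.

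**Working it through.** **Inputs**
- Primary-outcome planning values (power analysis under Fig. 1): "we expect a difference of 4 points on the IDS-SR"; the cited trial "found a difference of 5.3 points and a pooled standard deviation of 11.1 on the IDS-C after 10 weeks"; 80% power, alpha .05, 122 per group.
- Total randomized: 360 (Abstract), so 360/2 = 180 per arm if nobody is lost.
- CSQ-8: the article gives no SD, margin or sample size, so everything below is in SD units. Using 122 responders per arm is an assumption, borrowed from the primary outcome's completer number; 180 is the no-loss bound.

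**1. The plan's own figure**
- Standardized target effect: 4/11.1 = 0.36 SD.
- The normal approximation gives 121 per group. The noncentral t calculation gives 122, with power 0.8005. The stated 122 reproduces and is not in dispute.

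**2. How often the planned test would miss a real difference**

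For a true difference d with n per arm, the noncentrality is d × √(n/2) on 2n − 2 degrees of freedom. For example, at n = 122 and d = 0.2 it is 0.2 × √61 = 1.56, below the critical value of about 1.97. Power is 0.343, so the chance of non-significance is 1 − 0.343 = 0.657.

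| True difference | Non-significant, 122 per arm | Non-significant, 180 per arm |
|---|---|---|
| 0.1 SD | 88% | 84% |
| 0.2 SD | 66% | 53% |
| 0.3 SD | 35% | 19% |

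**3. What a non-significant result would leave open**
- 95% CI half-width = 1.96 × √(2/n): 0.25 SD at 122 per arm and 0.21 SD at 180.
- With 122 per arm, an observed difference of 0.20 SD would have an interval of 0.20 ± 0.25, that is −0.05 to 0.45 SD. It is non-significant, yet compatible with a difference larger than the trial's target effect on depression in SD units.

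**4. What an equivalence test could deliver**

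Two one-sided 5% tests, true difference zero, normal approximation: power = 2Φ(m/√(2/n) − 1.645) − 1, set to 0 where negative. At n = 122 and m = 0.4: 0.4/0.128 = 3.12; 3.12 − 1.645 = 1.48; Φ = 0.930; power = 0.86. All margins are assumptions.

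| Margin | Power, 122 per arm | Power, 180 per arm | n per arm for 80% |
|---|---|---|---|
| 0.2 SD | 0% | 20% | 429 |
| 0.3 SD | 51% | 77% | 191 |
| 0.4 SD | 86% | 97% | 108 |
| 0.5 SD | 98% | >99% | 69 |

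The 0.4 SD margin, the smallest in the table with more than 80% power at 122 per arm, exceeds the trial's target effect of 0.36 SD. With the tighter margins, equality could often not be shown even if it were true.

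**The case against.** The strongest reply is that the article never says how a non-significant CSQ-8 result will be read. A test for differences is a legitimate attempt to refute the expectation of equality, and no success criterion, sample size or trial decision depends on it. An unshown analysis plan might also add an interpretation or a margin. It is fair that no rule equating non-significance with equality is stated. What remains is that the only analysis named cannot support the hypothesis it belongs to, whatever is later said about reading it.

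A reader might infer more than the article supports:
- *That PMR's credibility as a control rests on this test.* The article bases it on cited literature about acceptance and helpfulness (Background; Progressive muscle relaxation), equal guidance by the same guides with call length, content and quality recorded (Guidance), and matched time and frequency of use (Discussion). Preference is to be examined by comparing dropout rates and reasons (Discussion).
- *That dissatisfied participants will be under-represented at T2, and that imputation would repair this.* The readable text gives no dropout rate. A loss of about 32% is only a back-calculation (1 − 244/360), and the direction of any bias is conjecture. Nor would imputing an outcome measured only once reliably correct loss driven by dissatisfaction.
- *That the switch from t-test to U-test is an error.* It is common practice, and objecting to it here is a matter of preference.

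**Conclusion.** The mismatch is real and visible in the text: an equality hypothesis that is not labelled exploratory is paired only with a two-sided difference test and no margin. A non-significant result could not support equal satisfaction. With 122 responders per arm, such a result would occur about two times in three at a true difference of 0.2 SD and about one time in three at 0.3 SD.

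These figures assume 122 responders per arm, with 180 as the upper bound, and a t-test on a standardized scale. The equivalence figures also assume margins that the article does not give.

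The point is limited to one secondary outcome and does not touch the primary analysis. It is also not a finding that the investigators will claim equality from non-significance. A reader might expect that from the pairing of hypothesis and test, but the article does not say it.

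**What to change.** Report the between-group CSQ-8 mean difference with its confidence interval. Claim equal satisfaction only if the 90% CI lies wholly inside an equivalence margin that is justified on the CSQ-8 scale and fixed before the T2 CSQ-8 data are seen. Any justification should address the fact that a margin of 0.4 SD or more is wider than the trial's target effect of 0.36 SD.

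Timing may rule this out. Recruitment ended in August 2018 (Trial status and review), the intervention lasts six weeks, the data section allows release once the last patient has finished it, and the article appeared in March 2019. If the T2 data are already open, or no margin can be justified, restate the hypothesis as an estimated difference with its confidence interval and make no claim of equality from a non-significant test.

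The cost is a change of wording and, at most, the choice of one margin; no further data are needed. The downside is that equality becomes harder to claim, and with a tight margin it may be out of reach at this sample size.
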